### Confidentiality {27}

Each participant in the intervention group will have a unique username and password in order to use the website, so, their privacy will not be violated in this regard. Research data is stored using a study identification code for each participant. The key to the identification code list will only be available to the research team during the study and will be documented and protected by FR after completion of the study. No participant identification information will be reported in the related publications. The technical support company for the website will be committed to maintaining the confidentiality of the users' information.

### Plans for collection, laboratory evaluation, and storage of biological specimens for genetic or molecular analysis in this trial/future use {33}

This is not applicable. This study has no laboratory evaluation or storage of biological specimens for genetic or molecular analysis, according to the researchers.

## Statistical methods

### Statistical methods for primary and secondary outcomes {20a}

All eligible participants in the study who will be randomly assigned to the groups will be considered the Full Analysis Set (FAS) that will make up the intent to treat analysis (ITT) population. The per-protocol population is a subset of the ITT population that has no violations of the study protocol (type of intervention and timing specified). Information on all quantitative data will be reported as mean (standard deviation) or median interquartile range (IQR), while qualitative data will be reported as frequency and percentage. We will compare the two groups to measure the effectiveness of the intervention and changes in the outcomes (depression, anxiety, and stress) over time using the repeated measures ANOVA test. The SPSS and STATA will be used for analysis of data.

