### Interventions

#### Explanation for the choice of comparators {6b}

All recruited participants will be randomly allocated to one of the intervention or control groups after baseline measurement. The intervention will not be applied to the control group during the study. They will receive routine care during the trial. If the intervention would be effective, at the end of the study, the control group participants can use the contents of the website and take advantage of the support group in order to ethical consideration.

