### Outcomes {12}

This study has three primary outcome variables (depression, anxiety, and stress) that are going to be measured by the DASS-21 scale three times during the study: before (T0), by the end of the first 3 months of the intervention (T1), and by the end of the second 3 months (T2) after the intervention. The effect of the web-based support group on depression, anxiety, and stress in the intervention and control groups will be assessed and compared before and after the intervention. The difference in the mean scores of the outcomes will be assessed.

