### Recruitment {15}

We will seek help from the South Tehran Health Center, hospitals, and other organizations in the area to cooperate to promote adequate enrolment. We will explain the aims and process of the study to their staff. We will ask them to advertise our study on virtual social networks and invite caregivers to participate in it. We will continue advertising until we reach the expected sample size. Furthermore, we will review the health records of elderly people in order to identify dependent elderly people and their caregivers, which were compiled in the South Tehran Health Center. Informal caregivers will be invited to participate according to inclusion criteria using telephone invitations. The purpose of the study, possible pros and cons of participation in the study, assurances of confidentiality, and the process of conducting the study will be explained to the caregivers. Also, the Mehrpishgan website will be introduced. If the individuals are interested in participating in the study and are eligible, they will receive a username and password and will be asked to complete the online consent form and the baseline measurement on the website. Before the commencement of the intervention, participants who will be in mild and moderate categories (based on DASS-21 scores) will be randomly assigned to one of the intervention or control groups.

Afterwards, participants in the intervention group will be asked to establish their activities in the web-support group for 6 months. At the end of the third month and sixth month, T1 and T2 assessments will be conducted in both intervention and control groups.

The control group will not be exposed to any intervention during the study. However, after completing the T2, they can use facilities of the website (Fig. 1).

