## Assignment of interventions: allocation

### Sequence generation {16a}

Randomization sequences will be generated using the online sealed envelope website (https://www.sealedenvelope.com/). To generate this randomized sequence, firstly a Software of Statistics and Data Sciences statistical (STATA) will be generated on sex variable; then, based on block size of four, all individuals will be allocated to two equal groups (20 blocks). A statistical consultant, independent of the research team, will generate a random sequence.

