## Data collection and management

### Plans for assessment and collection of outcomes {18a}

Data will be collected in three stages: before the intervention (T0), by the end of the first 3 months (T1), and by the end of the second 3 months (T2) after the intervention, using a 22-item demographic questionnaire and the online standard Persian-version of the 21-item DASS questionnaire.

The demographic questionnaire consists of 22-items including four main parts: (1) demographic characteristics of the caregivers including age, gender, educational status, occupation, marital status, place of residency, health status, and ethnicity; (2) activities of the caregivers including passing an elderly care training course, using comprehensive health care services, social activities, and types of services received for care assistance; (3) records on how to provide care, such as duration of care, daily life activities, instrumental daily life activities, number of people receiving care, and availability of the needed care; and (4) demographic characteristics of the elderly, including age, gender, health status, insurance, and ethnicity.

The DASS-21 Standard Depression, Anxiety, and Stress Questionnaire consists of 21 items prepared by Lovibond and Lovibond in 1995. The validity and reliability of the Persian-version of the questionnaire have been checked among Iranian population in some previous studies [20–22].The questionnaire is designed on a 4-point Likert scale: zero = at all (never), 1= low (sometimes), 2 = medium (often), and 3 = high (almost always) options. The lowest score for each question is zero, which indicates the best situation, while the highest score is three, which indicates the worst condition. To calculate the final score on each scale, the set of scores is multiplied by two, and the participant is placed in one of the normal, mild, moderate, severe, very severe subgroups specific to that scale. The points are calculated by the website plugin and are provided to the participant automatically at the end of the test.

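### The planned repeated measures ANOVA appears to treat the pre-randomisation DASS-21 score as a response; using it as a covariate, with one arm contrast named in advance, is a better-focused and usually more powerful analysis

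*Protocol article*

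**What the plan says.** Statistical methods {20a} names one analysis for the three primary outcomes. The groups will be compared for effectiveness and for "changes in the outcomes (depression, anxiety, and stress) over time using the repeated measures ANOVA test". It names no covariate and does not say which term of the ANOVA carries the intervention effect.

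Outcomes {12} says the outcomes are "measured by the DASS-21 scale three times during the study: before (T0), by the end of the first 3 months of the intervention (T1") and again at the end of the second three months (T2). The effect "in the intervention and control groups will be assessed and compared before and after the intervention", with no visit singled out. Plans for assessment {18a} repeats the schedule: "Data will be collected in three stages: before the intervention (T0"), then T1 and T2.

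On the order of baseline and allocation, Explanation for the choice of comparators {6b} says: "All recruited participants will be randomly allocated to one of the intervention or control groups after baseline measurement". Recruitment {15} adds that "participants who will be in mild and moderate categories (based on DASS-21 scores) will be randomly assigned".

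Sequence generation {16a} says the sequence "will be generated on sex variable; then, based on block size of four, all individuals will be allocated to two equal groups (20 blocks"). The sentence is garbled but reads as stratification by sex.

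Sample size {14} gives an effect size of 0.50, 5% alpha, 80% power, 63 per group, and 80 per group after 20% drop-out.

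**The concern.** A score taken before randomisation cannot carry a treatment effect. Its value lies in explaining variation in the later scores, and it does that best as a covariate. As a third level of the response, it leaves the analyst with two between-arm tests, neither well matched to the question.

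The group-by-time test asks whether the arms differ in any way in their pattern over three visits. It does not say at which visit, in which direction or by how much. The group main effect averages the arm difference over all visits, including T0, where the true difference is zero by design.

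At stake are power and a clear result. The sample size rests on a two-group difference of 0.50, but no stated ANOVA term or visit corresponds to that difference.

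**Working it through.** **The plan's own figure.** n per arm = 2(1.960 + 0.842)² / 0.5² = 62.8, so 63, as stated. The t-test version gives 64. Dividing by 0.8 for drop-out gives 79 from 63 and 80 from 64, so the stated 80 per arm reproduces. I use 64 completers per arm.

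**Inputs.** From the protocol: effect 0.5 SD, alpha 5%. Assumed: two-sided testing, SD 1 at each visit, and the same correlation r between any two visits (compound symmetry). The protocol gives no r, so I show 0.3, 0.5 and 0.7. Two effect patterns (T0, T1, T2) are used: constant (0, 0.5, 0.5) and gradual (0, 0.25, 0.5).

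**Group-by-time test.** Noncentral F on 2 and 2 × 126 = 252 df, with noncentrality (n/2) × Σ(d_t − d̄)² / (1 − r).
- Constant: Σ(d_t − d̄)² = 0.1667. At r = 0.5 the noncentrality is 32 × 0.1667 / 0.5 = 10.67.
- Gradual: Σ(d_t − d̄)² = 0.125. At r = 0.5 the noncentrality is 32 × 0.125 / 0.5 = 8.00.

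**Group main effect over T0–T2.** The estimand is the mean of the three differences: (0 + 0.5 + 0.5)/3 = 0.333 for a constant effect, (0 + 0.25 + 0.5)/3 = 0.25 for a gradual one. The variance of a person's mean is (1 + 2r)/3, which is 0.667 at r = 0.5. The standardised effect is then 0.333 / √(2 × 0.667/64) = 2.31.

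**Baseline-adjusted difference at T2.** The residual variance is 1 − r², which is 0.75 at r = 0.5. The standardised effect is 0.5 / √(2 × 0.75/64) = 3.27. Both patterns have 0.5 SD at T2, so power is the same for both.

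| Power, 64 per arm | r = 0.3 | r = 0.5 | r = 0.7 |
|---|---|---|---|
| Group-by-time (2 df), constant | 0.69 | 0.84 | 0.97 |
| Group-by-time (2 df), gradual | 0.56 | 0.71 | 0.91 |
| Group main effect, constant (0.33 SD) | 0.73 | 0.63 | 0.55 |
| Group main effect, gradual (0.25 SD) | 0.49 | 0.41 | 0.35 |
| Adjusted difference at T2, either pattern | 0.84 | 0.90 | 0.98 |

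**Other choices of visit.** The adjusted difference in the mean of T1 and T2 has variance (1 + r)/2 − r², which is 0.50 at r = 0.5. For a constant effect its power is 0.96, 0.98 and above 0.99. For a gradual effect the mean difference is 0.375 SD and power is 0.80, 0.85 and 0.94. At T1 alone a gradual effect is only 0.25 SD, and adjusted power is 0.31, 0.37 and 0.50. The choice of visit therefore matters.

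**Sex.** If sex explains 1%, 3% or 6% of the variance (assumed), then with 63 per arm the power of a comparison at T2 without T0 is 0.805, 0.813 or 0.825 with sex in the model, against 0.802, 0.805 or 0.809 without. The type I error without sex is 0.049, 0.047 or 0.043. Omitting it costs at most about 2 points of power and is slightly conservative.

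**The case against.** **The text points to the valid test.** A reader might infer that T0 dilutes the trial's treatment effect by a third. That holds only for the group main effect, which the protocol does not select. Comparing groups on change over time, before and after, fits group-by-time better, and T0 does not dilute that term. This objection stands, and the main-effect figures are a conditional risk only.

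**The power loss is not general.** For a constant effect at r = 0.5 the group-by-time test has 0.84, above the planned 80%, and at r = 0.7 it almost matches the adjusted contrast (0.97 against 0.98). Part of the gap comes from setting a 2-df test against a single contrast. At r = 0.5 with a constant effect, the ANOVA's own 1-df contrast, mean of T1 and T2 minus T0, has variance 1.5(1 − r) = 0.75, the same as the adjusted contrast at T2. This also stands, but the protocol names no such contrast. The loss is largest at low r, which randomising only mild and moderate scorers makes more plausible.

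**T0 as a repeated level is inferred.** The protocol does not state it outright. It is still the natural reading of three measurements, a before-and-after comparison and change over time.

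**Sex.** A reader might infer that leaving out the stratification factor biases or blurs the contrast. It does not. The point also rests on a garbled sentence and on silence in a condensed article, whose covariates may be set out in an analysis plan not shown.

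**Time effect.** The hypothesis under Objectives {7} is worded as a before-and-after difference, so a reader might infer that the time effect could be taken as the result. Statistical methods {20a} says the two groups will be compared, which rules that out.

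**Conclusion.** The point holds as a recommended improvement in efficiency and clarity. It does not show that the planned analysis is invalid. On the natural reading, a pre-randomisation score sits in the response, and the stated model leaves open which term, visit and estimate measure the intervention.

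Against the group-by-time test, the adjusted contrast at T2 gains about 1 to 15 points of power for a constant effect (0.98 against 0.97 at r = 0.7; 0.84 against 0.69 at r = 0.3) and about 7 to 28 points for a gradual one (0.98 against 0.91; 0.84 against 0.56). It also gives one estimate with a confidence interval. Against the group main effect the gain is larger, but only if that term were used.

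These sizes rest on assumed correlations, compound symmetry, two-sided testing and 64 completers per arm. The advantage is for T2, or for the mean of T1 and T2; it would not hold at T1 if the effect builds slowly.

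**What to change.** Amend Statistical methods {20a} so that, for each of the three scales, T1 and T2 are the responses in a linear mixed model. The fixed effects are arm, visit, arm × visit, T0 score and T0 × visit, with sex added as the randomisation stratum for a minor gain in precision. Take the effect of the intervention from the baseline-adjusted arm difference with its 95% confidence interval at one target named before the data are analysed: T1, T2 or their mean. Report the other visit from the same model.

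The choice of target belongs to the trial team. Outcomes {12} gives T1 and T2 equal standing, and the two phases differ: the Intervention procedure has a facilitator lead the first three months and group members the second.

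The change needs no new data, and SPSS and STATA, already named, can fit the model. It is not purely a matter of wording. The team must choose the target, and the regression imputation in section {20c} must be reconciled with a mixed model that uses all observed T1 and T2 scores.

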### Interim analyses {21b}

This is not applicable. There are no interim analyses planned.

### Methods for additional analyses (e.g., subgroup analyses) {20b}

This is not applicable. There are no subgroup analyses planned.

### Methods in analysis to handle protocol non-adherence and any statistical methods to handle missing data {20c}

We will use the intention to treat (ITT) analysis approach. For missing data, simple linear regression methods will be used to replace the missing data (imputation).

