### Sample size {14}

The study population consists of informal primary caregivers of the elderly in the South Tehran, who have the willingness to participate. The sample size has been calculated using PASS 15.0.5 software. Based on literature [18] and using Cohen’s formula (expecting the average effect size) with a coefficient = 0.5 φ [19], for both of the intervention and control groups (63 people), taking into account the power of 80. The effect size is 0.50 and the significance level (alpha) will be 5%, the probability of drop-out and withdrawal of the study is 20%, equivalent to 80 people in each group, and the total will be 160 people.

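### Replacing missing DASS-21 scores by simple linear regression and then running a repeated measures ANOVA gives either standard errors that are too small or an effect pulled towards zero, depending on how the regression is fitted

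*Protocol article*

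**What the plan says.** Section {20c} of the protocol article commits to ITT ("We will use the intention to treat (ITT) analysis approach") and then gives the rule for gaps: "For missing data, simple linear regression methods will be used to replace the missing data (imputation". Section {20a} compares the groups and the "changes in the outcomes (depression, anxiety, and stress) over time using the repeated measures ANOVA test". DASS-21 is scored at T0, T1 (three months) and T2 (six months), and section {12} makes all three scales primary outcomes. Section {14} allows for loss: "the probability of drop-out and withdrawal of the study is 20%, equivalent to 80 people in each group".

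The article does not say which predictors enter the regression, whether it is fitted within arm or on both arms together, or how many completed data sets are made. It names no variance correction, mixed model or multiple imputation.

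**The concern.** A regression prediction is not an observation. A filled-in score has no residual scatter, and the error in the fitted line is ignored. The ANOVA nevertheless counts it as a full observation. The sample size was inflated so that about 64 per arm would remain after drop-out; the imputation rule then analyses 80 per arm as if nobody had been lost.

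What goes wrong depends on a choice the article leaves open. If each arm has its own regression, or arm is a predictor, the estimate is unbiased but its standard error is too small. If one regression is fitted across both arms without arm, the filled-in scores of the two arms differ too little and the group difference shrinks. The rule governs the ITT result for all three primary outcomes.

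A later SAP could add detail, but the protocol already names this method, so the point concerns a stated rule and not an omission.

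**Working it through.** **Inputs from the protocol article.** Effect size 0.50, alpha 5%, power 80%, 63 per arm raised to 80 for 20% drop-out ({14}); assessments at T0, T1 and T2 ({12}); repeated measures ANOVA ({20a}); regression replacement ({20c}).

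**Assumptions.** Two-sided test (not stated, but it reproduces 63); scores missing completely at random and equally in both arms; equal correlation r between visits, 0.3 to 0.7; SD 1; the same true effect at T1 and T2.

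**The plan's own figure.** n = 2 × (1.960 + 0.842)² / 0.50² = 62.8, so 63 per arm. Then 63/0.8 = 78.75, so 79; the t-test version gives 64, and 64/0.8 = 80. The sample size reproduces and is not in dispute. Missing per arm: d = 0.20, or 16 of 80.

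**(a) Regression within arm, or with arm as a predictor.** Let σ² be the residual variance and N = 80.
- True variance of the adjusted T2 difference: 2σ² / [N(1 − d)], because only N(1 − d) scores per arm carry information.
- Reported variance: about 2σ²(1 − d) / N, because the filled-in scores add nothing to the residual sum of squares but do add to the count.
- Reported SE / true SE = 1 − d = 0.80, whatever r is.
- Actual type I error = 2 × [1 − Φ(1.96 × 0.80)] = 11.7%.

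The same formula for other missing fractions:

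| Missing | SE ratio | Type I error |
|---|---|---|
| 5% | 0.95 | 6.3% |
| 10% | 0.90 | 7.8% |
| 20% | 0.80 | 11.7% |
| 30% | 0.70 | 17.0% |

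Simulation at 80 per arm with 16 per arm missing T2:
- Baseline-adjusted T2 comparison: type I error 10 to 13%. At r = 0.5 the reported SE is 0.122 against a true 0.154.
- Group-by-time interaction of the repeated measures ANOVA, the test nearest to the plan: 8 to 9% in runs where drop-outs missed only T2, and 9.9 to 11.1% in runs where half of them also missed T1. Across all runs the range was 8 to 12%.

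**(b) One regression on both arms, without arm.** Under the null, type I error was 4.2 to 5.4%, so it is not inflated. The bias appears when there is an effect.
- Predictor T0: randomisation balances T0, so the filled-in scores show no arm difference on average. Expected estimate = 0.80 × 0.50 + 0.20 × 0 = 0.40, a 20% loss. Simulation gave 0.40, with 95% interval coverage of 0.83 to 0.91.
- Predictor T1 where available: T1 already carries an effect. The pooled slope is (r + 0.50²/4) / (1 + 0.50²/4) = (r + 0.0625) / 1.0625.
  - r = 0.7, T1 complete: slope 0.718; estimate 0.40 + 0.20 × 0.50 × 0.718 = 0.47, a loss of about 6%.
  - r = 0.3, half the drop-outs also missing T1 and filled from T0: slope 0.341; estimate 0.40 + 0.10 × 0.50 × 0.341 = 0.417, a loss of about 17%.

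**(c) If one random residual were added to each prediction, by arm.** The true variance rises by the factor 1/(1 − d) + d = 1.25 + 0.20 = 1.45 relative to the reported one. The SE ratio is 1/√1.45 = 0.83 and type I error about 10%. Adding scatter to a single imputation does not repair it.

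**Reference.** Baseline-adjusted analysis of the 64 observed per arm, under the same assumptions, gave type I error 4.5 to 5.1%, coverage 0.947 to 0.955 and a mean estimate of 0.50.

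**The case against.** The article does not say that one fitted value per gap is used, nor that it is treated as observed. Regression is also the usual engine inside multiple imputation of continuous scores. That is fair: single imputation is the plain reading of {20c} with {20a}, not quoted text. But nothing in the article points to repeated imputation or a variance correction.

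A reader might infer that the rule inflates false positives whatever is done. The documents do not support this. A simple regression in the strict sense has one predictor, which suggests that arm is not in it; on that reading alpha stays near 5% and the harm is a diluted effect. The inflation needs arm-specific fits, which {20c} does not state. Nor do the two harms add up: one or the other arises.

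A reader might also infer that pooled filled-in scores never contain a treatment effect, or that a false-positive rate of about 12% applies to any test in the plan. The first holds only when T0 is the predictor. The 11.7% comes from a baseline-adjusted T2 comparison; the interaction gives about 8 to 12%, and the group main effect was hardly touched (5 to 6%) when only T2 was missing.

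Finally, 20% is a planning allowance and not an observed rate. Section {18b} provides online questionnaires, SMS reminders and researcher contact. With 5 or 10% missing, the problem is smaller, as tabulated. These points limit the size; none of them makes the stated rule valid.

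**Conclusion.** The concern holds in this form: read plainly, the imputation rule in {20c} combined with the ANOVA in {20a} gives wrong inference on either way of fitting the regression. At 20% missing, within-arm fitting gives a type I error of about 8 to 12% for the planned interaction. Pooled fitting without arm keeps it near 5% but loses about 20% of the effect with T0 as predictor, or about 6 to 17% with T1 where available.

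These sizes rest on the assumed missingness, visit correlations and T1 loss listed above. The 0.80 ratio for the baseline-adjusted comparison does not depend on the correlation. The lack of a sensitivity analysis for scores missing not at random is not part of this error, since such analyses are commonly left to a SAP.

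**What to change.** In {20a} and {20c}, replace single regression imputation by one of the following:
- a likelihood-based linear mixed model on all observed T1 and T2 scores, with T0 score, sex, arm, time and arm × time, which needs no imputation if scores are missing at random; or
- multiple imputation with arm, sex, T0 and T1 in the imputation model, combined by Rubin's rules.

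Section {6b} places the baseline measurement before randomisation, so T0 should be available for everyone. A sensitivity analysis for data missing not at random is optional.

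The cost is a change of wording in two sections, slightly more analysis work in the software already named (SPSS, STATA), and a wider, honest confidence interval. In the simulation at r = 0.5, the SE of the T2 comparison goes from a reported 0.122 to about 0.154. The planned power survives: with 64 observed per arm, the baseline-adjusted comparison detected an effect of 0.50 in 84% (r = 0.3) to 97% (r = 0.7) of runs. Design, recruitment and data collection do not change.
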